**Method and analysis::**

A randomized, nonblinded, controlled trial will be carried out by recruiting a total of 66 eligible allergic rhinitis patients who fulfill the inclusion criteria from a university health center. The subjects will be randomly assigned into 2 groups: intervention group receiving facial candling treatment and control group (no treatment given). Samples of blood and nasal mucus will be collected right before and after intervention. Samples collected will be analyzed. The primary outcomes are the changes in the level of SP in both blood and mucus samples between both groups. The secondary outcomes include the levels of inflammatory mediators (ie, tumor necrosis factor alpha, interleukin (IL)-3, IL-5, IL-6, IL-10, and IL-13) and the severity of allergic rhinitis symptoms as measured by a visual analogous scale and QoL using the Rhinitis Quality of Life Questionnaire (RQLQ).

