### Outcome measures

2.4

The primary outcome measure for this study is the difference in the level of SP in blood and nasal mucus samples in pre- and postintervention. The secondary outcome measures include the levels of inflammatory mediators (tumor necrosis factor alpha [TNF-α], IL-3, IL-5, IL-6, IL-10, and IL-13) in both blood and nasal mucus samples. Other secondary outcome measures also include the visual analogous scale (VAS) score (indicating the pain intensity) and the Rhinitis Quality of Life Questionnaire (RQLQ).

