### Sample size calculation

2.6

The sample size is calculated using Power and Sample Size software 3.1.2 version. The difference between the mean values of the intervention and control groups, and the standard deviation (postmassage) of SP levels^[27]^ will be used as parameters for sample size calculation given there is no previous finding of the immediate effect of facial candling treatment on SP. The mean levels of SP in the intervention group and control group are 50.43 and 56.27 pg/mL, respectively (the difference in the mean values between the experimental and control groups is 5.84 pg/mL).^[27]^ The type I error probability associated with this test of the null hypothesis is 0.05. A sample of 33 experimental subjects and 33 control subjects is therefore required to reject the null hypothesis that the population means of the experimental and control groups are equal, with a probability (power) of 0.8.

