### Data analysis plan

2.7

Data will be analyzed using SPSS software version 20.0. Mean, standard deviation, and range will be calculated for each variable. Data will be tested for normality; paired *t* test will be used (if the distribution is normal) or Mann–Whitney (if the distribution is skewed) to measure the differences pre- and postintervention within and between groups for every outcome measure. A *P* value of less than 0.05 will be used to show that the result is statistically significant.

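### Section 2.7 lets normality alone choose between a paired t test and Mann–Whitney for both within-arm and between-arm comparisons, so each test is mismatched to one of its two uses and no suitable between-arm test is named for normal data

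*Protocol article*

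**What the plan says.** Section 2.7 (Data analysis plan) is the only place in the protocol article where tests are named. For normal data a paired *t* "test will be used (if the distribution is normal"; for skewed data the sentence continues "or Mann–Whitney (if the distribution is skewed) to measure the differences pre- and postintervention within and between groups for every outcome measure". No independent-samples *t* test, Wilcoxon signed-rank test or ANCOVA appears anywhere.

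The rest of the article sets out the comparisons these tests must serve:

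- Design (abstract): "The subjects will be randomly assigned into 2 groups: intervention group receiving facial candling treatment and control group (no treatment given"). No matching of patients across arms is described there or in Section 2.1.
- Measurement (abstract): "Samples of blood and nasal mucus will be collected right before and after intervention".
- Primary outcome (abstract): "The primary outcomes are the changes in the level of SP in both blood and mucus samples between both groups".
- Primary outcome (Section 2.4): "the difference in the level of SP in blood and nasal mucus samples in pre- and postintervention", with no mention of groups.
- Sample size (Section 2.6): the trial is sized to reject "the null hypothesis that the population means of the experimental and control groups are equal", with 33 patients per arm and power 0.8.

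**The concern.** A paired *t* test needs a natural link between the two members of each pair. That link exists between a patient's own pre and post values, but not between a candled patient and a control patient. Mann–Whitney is the reverse: it needs two independent samples, which the arms are and the pre/post values of one arm are not. Section 2.7 gives both tests both jobs and lets normality choose, so whichever branch is taken, one of the two comparisons gets an unsuitable test.

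The normal branch matters most, because it leaves the primary between-arm comparison without a usable test. An analyst then has to improvise. One route is to pair patients by row order. The other, more natural in practice, is to run a paired test in each arm and compare the two verdicts. That second route does not test the hypothesis the trial was sized for, and it can easily suggest an effect in a nonblinded trial whose controls only rest.

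**Working it through.** **1. What Section 2.6 sized.** Difference in means: 56.27 − 50.43 = 5.84 pg/mL, as printed. The SD is not printed, so 33 per arm can only be solved backwards. I assume a two-sided alpha of 0.05, since the article does not state sidedness. For two independent means,

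SD = 5.84 × √(33/2) / (1.960 + 0.842) = 5.84 × 4.062 / 2.802 ≈ 8.47.

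With the *t* distribution in place of the normal, the SD is 8.34. This is an independent-groups calculation. SD 8.34 is used below as an assumption.

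**2. The tests against their uses.**

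| Branch | Within arm (same patients) | Between arms (different patients) |
|---|---|---|
| Normal: paired *t* | suitable | no pairs exist |
| Skewed: Mann–Whitney | ignores pairing | suitable |

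**3. Paired *t* test across arms, pairs formed arbitrarily** (20,000 simulated trials, 33 per arm, SD 8.34).

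| | Type I error | Power at 5.84 pg/mL |
|---|---|---|
| Independent *t* | 0.049 | 0.800 |
| Paired *t*, arbitrary pairs | 0.049 | 0.786 |

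Under the planned effect, two arbitrary pairings of the same data gave different significance verdicts in 5.9% of trials. If the arms end with unequal numbers, some patients cannot be paired and drop out.

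**4. Separate paired *t* tests in each arm, verdicts compared.** Let both arms have the same true change, 0.35 SD of the change, so there is no treatment effect. With 33 patients the noncentrality is 0.35 × √33 = 2.01, and each arm is significant with probability about 0.50. Exactly one arm is then significant with probability 2 × 0.50 × 0.50 = 0.50, and candling alone with probability 0.25. Simulation gave 0.501 and 0.250. A direct between-arm *t* test on the same data was significant in 5.2% of trials.

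**5. Mann–Whitney on pre versus post within an arm.** The test's null variance assumes independence. Positive correlation makes the true variance smaller, so the test rejects too rarely. With n = 33, assumed correlations and a 0.5 SD shift for power:

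| Correlation | Type I error | Power, Mann–Whitney | Power, signed-rank |
|---|---|---|---|
| 0.3 | about 2% | about 50% | 61% to 63% |
| 0.5 | 0.8% | about 50% | 78% to 79% |
| 0.7 | 0.1% to 0.15% | about 50% | 94% |

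The ranges are spread between simulation runs. Log-normal data with log-scale SD 0.6 and a shift of 0.3 (0.3/0.6 = 0.5 SD) show the same pattern. At correlations 0.3, 0.5 and 0.8, type I error was 0.024, 0.008 and 0.0005. Power was 0.50, 0.49 and 0.51, against 0.60, 0.74 and 0.98 for signed-rank.

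**6. Which between-arm test to name.** Section 2.7 analyses pre/post differences, so the fair comparator for ANCOVA is a *t* test on change. If ρ is the pre/post correlation and the SD is the same at both times, the working SD is

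- change score: 8.34 × √(2(1 − ρ))
- ANCOVA: 8.34 × √(1 − ρ²)

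| ρ | SD, change | Power, change | SD, ANCOVA | Power, ANCOVA |
|---|---|---|---|---|
| 0.3 | 9.87 | 66% | 7.96 | 84% |
| 0.5 | 8.34 | 80% | 7.22 | 90% |
| 0.7 | 6.46 | 95% | 5.96 | 97.5% |

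These use the noncentral *t* with 33 per arm and a difference of 5.84 pg/mL.

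**The case against.** **The intent can be guessed.** A reader might take the sentence as paired *t* within arms and Mann–Whitney between them. The text does not allow it: each test carries its own distributional condition, and both are given both uses.

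**The primary outcome may be a within-patient change.** Section 2.4 defines it as a pre/post difference without mentioning groups, and a paired *t* test fits that. This is a fair point about an unsettled definition. But the abstract places the contrast between groups, and Section 2.6 sizes that contrast, so the plan still needs a between-arm test.

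**The primary test is not statistically invalid.** A reader might infer that a paired *t* test across arms has the wrong error rate. The figures do not support this: size is 0.049, and power falls only from 0.800 to 0.786. What is left is an undefined pairing and a verdict that depends on row order. Similarly, Mann–Whitney within arms is conservative and creates no excess false positives, and Mann–Whitney between arms is appropriate, so the skewed branch is sound for the primary contrast. Dropout from unequal arms is a contingency, since 33 and 33 are planned.

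**Not naming a baseline covariate is no error in itself.** That stands: an article may leave it to an analysis plan that is not shown, and change scores already use baseline. ANCOVA is recommended here only because the sentence has to be rewritten anyway.

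**Log-transformation.** Nothing in the documents shows that SP is skewed, and a ratio of geometric means would depart from the 5.84 pg/mL arithmetic difference in Section 2.6. It is optional and not part of the correction.

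**Conclusion.** Wrong as written. Section 2.7 fixes a rule that does not match tests to comparisons; this is not detail left out by a condensed article. For normal SP, no suitable test is named for the between-arm primary contrast, and Section 2.7 does not follow the independent-groups hypothesis of Section 2.6.

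The size of the problem depends on what the analyst does. Arbitrary pairing costs little in error or power but leaves the verdict non-unique in about 6% of trials. Comparing within-arm verdicts is the serious risk: about a 50% chance of significance in exactly one arm when both change equally by 0.35 SD of the change. Mann–Whitney within arms loses roughly 10 to 45 percentage points of power against signed-rank over correlations 0.3 to 0.7.

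The mismatch rests on the text alone. The sizes rest on assumptions, because the article gives no SD or pre/post correlation: SD 8.34, correlations 0.3 to 0.8, a common change of 0.35 SD, and two-sided alpha. The sample size calculation is not called into question by this point.

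**What to change.** Replace the test sentence in Section 2.7 with wording such as:

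> The primary comparison for each outcome is between arms, by ANCOVA of the post-intervention value on arm with the pre-intervention value as covariate, reported as an adjusted mean difference with 95% confidence interval. If the data are clearly skewed, the arms are compared by Mann–Whitney on change scores. Within-arm changes are reported with a paired *t* test or Wilcoxon signed-rank test as description only and are not evidence of efficacy.

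The least change that cures the fault is an independent-samples *t* test on change in place of ANCOVA. ANCOVA is preferable: under the assumptions above, the change-score test falls short of the planned 80% power when the pre/post correlation is below 0.5, while ANCOVA does not. ANCOVA in pg/mL also keeps the effect on the scale used in Section 2.6. Section 2.4 should be reworded to state the between-arm contrast, as the abstract does.

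The cost is wording only. Pre and post values are already collected, and N stays at 33 per arm because Section 2.6 already assumes independent groups. The change should be dated and made before results by arm are examined.

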**Conclusion::**

Facial candling is one of the unique treatments using candles to reduce the severity of symptoms and inflammation. This is the first ever study conducted on facial candling that will give rise to new knowledge underlying the effects of facial candling on severity of symptoms and inflammation relief mechanism mediated by substance P and inflammatory mediators.

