### Instruments

2.5

All samples will be analyzed individually using commercial human enzyme-linked immunosorbent assay kits (Table 1). The VAS is a measurement of pain and symptom intensity and has been found to be acceptable to patients and valid.^[25,26]^ The scale ranges is from “0” to “10” with a different facial expression whereby 0 represents “no pain/symptom” and 10 represents the “worst possible pain/symptom.” In this study, patients will be asked to rate their pain and symptom severity using the VAS pre- and postintervention. RQLQ will also be used to assess the disease-associated problems of the participants in 7 aspects of daily life: activities, sleep, nonnose/eye symptoms, practical problems, nasal symptoms, nose symptoms, and emotional symptoms. The score of each of the item is graded into 0 to 6. The total score of the 7 items will be calculated for every participant at baseline (1 day before) and 1 day after the intervention.

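### One unadjusted P<0.05 threshold is fixed for all 14 secondary outcomes, within and between groups, although the article expects mechanism and symptom conclusions from them

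*Protocol article*

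**What the plan says.** Section 2.4 (Outcome measures) makes substance P (SP) in blood and mucus the primary outcome. The secondary outcomes are the "levels of inflammatory mediators (tumor necrosis factor alpha [TNF-α], IL-3, IL-5, IL-6, IL-10, and IL-13) in both blood and nasal mucus samples". The section then adds: "Other secondary outcome measures also include the visual analogous scale (VAS) score (indicating the pain intensity) and the Rhinitis Quality of Life Questionnaire (RQLQ". Section 2.5 (Instruments) reduces the RQLQ to one number per visit: "The total score of the 7 items will be calculated for every participant at baseline (1 day before) and 1 day after the intervention".

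Section 2.7 (Data analysis plan) uses its tests "to measure the differences pre- and postintervention within and between groups for every outcome measure". It then says that a P "value of less than 0.05 will be used to show that the result is statistically significant". The same threshold therefore covers primary and secondary outcomes, and within-group and between-group tests.

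The abstract's conclusion says that the study will bring new knowledge about the "effects of facial candling on severity of symptoms and inflammation relief mechanism mediated by substance P and inflammatory mediators". The Discussion (section 3) also links relief to reduced SP and mediators, and section 3.1 presents the study as able to supply evidence for prescribing candling.

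**The concern.** Testing many secondary outcomes without adjustment is tolerable when they are presented as exploratory. Here they are not. The mediators and the symptom and quality-of-life scores are what the article intends to use to explain how candling works and whether patients feel better, and the stated threshold treats each of them as a stand-alone test at 5%.

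With 14 such tests, a treatment with no effect has a substantial chance of producing at least one result that the plan permits to be called statistically significant. Nothing names a leading mediator or a leading fluid, so an isolated cytokine change could be reported as support for the mechanism even if SP shows no difference.

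**Working it through.** **Plan's own figure.** The article states no familywise error rate, so there is none to reproduce. The sample size of 33 per arm rests on SP alone and does not bear on this point.

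**Inputs**
- Threshold per test: 0.05 (section 2.7), taken as two-sided.
- Secondary outcomes (section 2.4): 6 mediators × 2 fluids = 12, plus VAS and RQLQ = 14. VAS is counted as one score and RQLQ as one total (section 2.5). Separate pain and symptom ratings, or separate RQLQ domains, would raise the count.
- Patients: 33 per arm (section 2.6).
- Correlation r between outcomes: not given. Assumed equal for all pairs, at 0, 0.3, 0.5 and 0.7.

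**Step 1. Between-arm tests, independent outcomes.** One test per outcome, each with true size 5%:
- 12 mediators: 1 − 0.95^12 = 0.460
- 14 secondaries: 1 − 0.95^14 = 0.512
- Only results favouring candling, taken as one tail of 0.025 per outcome: 1 − 0.975^14 = 0.298

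**Step 2. Expected number of false positives.** This does not depend on correlation: 14 × 0.05 = 0.70 significant between-arm results, of which 14 × 0.025 = 0.35 favour candling.

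**Step 3. Correlated outcomes.** Normal change scores were simulated under no effect with common correlation r. Z- and t-based versions agree to within about one percentage point. The last column counts an outcome if either its between-arm test or its pre/post test within the candling arm is significant, and assumes no true pre/post change in that arm.

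| r | Between arms, either direction | Between arms, favouring candling | Between arms or within candling, either direction |
|---|---|---|---|
| 0 | 51% | 30% | 70% |
| 0.3 | 44% | 23% | 63% |
| 0.5 | 35% | 18% | 52% |
| 0.7 | 25% | 13% | 38% |

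At r = 0.1 the first column is 50.2%, and at r = 0.2 it is 47.5%. It therefore falls below one half once r passes about 0.1.

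**Step 4. With a correction.** Holm's first step over the 12 mediators is 0.05/12 = 0.0042. If the mediators and the VAS/RQLQ pair are two families, each held at 5%, the chance of any false claim across both is at most 0.05 + 0.05 = 10%.

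**The case against.** **An unseen analysis plan may deal with multiplicity.** An article need not print every detail, and silence alone would not be a finding. But section 2.7 is not silent: it states the threshold and applies it to every outcome. A plan that adjusted the secondaries would have to override that sentence. The objection does not remove the point, but it does limit its weight.

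**These are secondary outcomes.** The article separates primary from secondary and sizes the trial on SP alone. Unadjusted secondary tests are common. This stands, and it makes the point a cheap improvement, not a threat to the primary analysis.

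**Two stronger readings are tempting and are not supported.**
- A reader might infer that a null trial would more likely than not show a significant secondary result. For between-arm tests this holds only near independence, up to r of about 0.1. The outcomes come from the same patients and samples, so independence is the least favourable assumption. Exceeding one half at higher correlations requires adding the within-candling tests and assuming no true pre/post change in that arm. An inert treatment does not guarantee that: patients lie down during the session (section 2.2), and the collection device itself stimulates secretions (section 2.3). Counting only results that favour candling, the between-arm chance is 30% at most.
- A reader might also infer that the plan lets any one mediator establish inflammation relief. No section writes such a rule. Section 2.7 sets a threshold per test and no success criterion for the mediators as a group. The figures above describe how often at least one significant result would appear, not how often a written claim rule would be met.

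**Conclusion.** The point holds as a cheap improvement. The plan fixes one unadjusted 5% threshold for 14 secondary outcomes and intends to draw conclusions from them. Under no effect, the between-arm familywise error is roughly 25% to 51% over the correlations tried, which is five to ten times the nominal rate. In the direction that favours candling it is about 13% to 30%. The within-candling tests add to this, but their contribution depends on an assumption about that arm which the article does not support.

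The figures rest on the count of 14, two-sided tests of true size 5%, normal change scores and equal correlations. The correlations are assumed throughout. The conclusion does not depend on where in that range the truth lies, because the error exceeds 5% at every value examined.

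**What to change.** In section 2.7, replace the blanket threshold with a rule for the secondary outcomes:

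1. Base inference for each secondary outcome on the between-arm comparison only. Report within-arm changes descriptively.
2. Either treat the 12 mediator comparisons as one family, using Benjamini-Hochberg with the false discovery rate at 5% or Holm, and test VAS and RQLQ by Holm; or label all secondaries exploratory and report between-arm differences with 95% confidence intervals and no significance label.
3. Claim an effect on a mediator only if it passes that rule, and align the abstract conclusion and Discussion with it.

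Making secondary claims conditional on success for SP is a further option, but a debatable one, and the point does not depend on it.

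The cost is wording: no new patients, samples or assays. The downside is that an isolated mediator with P just under 0.05 could no longer be called significant. Under Holm, the smallest of the 12 P values would have to be about 0.004 or less.

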### Trial monitoring

2.8

The interim data and findings will be reported to the UiTM Research Ethics Committee. This is an investigator-initiated trial evaluating current. As there is minimal additional risk from a normal standard of care, a trial Data Safety and Monitoring Board was not deemed necessary.

## Discussion

3

There is growing awareness that the knowledge of SP may help to develop new methods to treat pain and inflammation.^[19,28,29]^ For example, SP and inflammatory mediators appear to play a role in allergic rhinitis.^[30,31]^ Recently, the role of SP in the pathophysiology of clinical syndromes such as inflammatory rhinitis and diseases with chronic inflammatory pain in general is becoming clearer.^[32]^ It can be expected that the development of drugs and interventions aimed at the modulation of SP will be able to help in treatment of pain associated with these diseases. Previous study used the level of SP in nasal mucus to indicate the severity of pain in many chronic pain conditions, because the amount of SP is significantly greater in nose mucus than in plasma.^[33]^

As there is no previous finding related to facial candling, we explored studies that trialed effectiveness of other complimentary treatment methods. For example, 23 patients (19 were serologically tested positive for allergic diseases) with persistent allergic rhinitis were treated with 4 acupoint herbal plaster applied using the moxibustion technique. Clinical outcomes measured using the RQLQ indicated that the patients tested positively for allergic disease responded better to the treatment. Furthermore, IL-13 immune response was downregulated in that particular group of patients.^[22]^ Similarly, another study demonstrated the effectiveness of subcutaneous injectable immunotherapy in treating the sinus inflammation and pain in 281 allergic rhinitis patients. The subcutaneous immunotherapy as treatment of allergic rhinitis led to a reduction in all symptoms studied, improving the QoL of patients.^[34]^ Antiinflammatory effects of acupuncture and their relevance to allergic rhinitis have also been examined.^[35]^ Acupuncture has been shown to significantly reduce histamine-induced symptoms of allergic rhinitis. Furthermore, the study showed that there is significantly reduce of IL-4 and IL-10 in allergic rhinitis patients as acupuncture treatment has been applied^[36]^ and their finding was supported by Petti et al,^[37]^ who revealed the significant decrease of IL-10 immediately after acupuncture treatment. Interestingly, they showed unpredicted significant decrease of IL-2 and no significant changed in IL-6.

This is the first ever study conducted regarding facial candling treatment with the severity of symptoms (including nociception and pain) and inflammatory mediator. The present project will give rise to new knowledge underlying the immediate effect of facial candling on symptoms severity and inflammation relief mechanism caused by the reduction of SP and inflammatory mediators. Apart from that, this study will elucidate the extent to which facial candling can diminish the symptoms of allergic rhinitis thus improving patient's functions. Facial candling can be an alternative treatment approach and most likely popular intervention because it is a noninvasive technique which provides relaxation in face as well as reduction in allergy. Furthermore, the study helps the local traditional medicine practitioner generate new interests on treatment of other pain and inflammatory area such as osteoarthritis and migraine.

